## Abstract

**Introduction:**

Oxygen is the most commonly administered drug to mechanically ventilated critically ill adults, yet little is known about the optimum oxygen saturation (SpO_2_) target for these patients; the current standard of care is an SpO_2_ of 96% or above. Small pilot studies have demonstrated that permissive hypoxaemia (aiming for a lower SpO_2_ than normal by using a lower fractional inspired oxygen concentration (FIO_2_)) can be achieved in the critically ill and appears to be safe. This approach has not been evaluated in a National Health Service setting. It is possible that permissive hypoxaemia may be beneficial to critically ill patients thus it requires robust evaluation.

**Methods and analysis:**

Targeted OXygen therapY in Critical illness (TOXYC) is a feasibility randomised controlled trial (RCT) to evaluate whether recruiting patients to a study of permissive hypoxaemia is possible in the UK. It will also investigate biological mechanisms that may underlie the links between oxygenation and patient outcomes. Mechanically ventilated patients with respiratory failure will be recruited from critical care units at two sites and randomised (1:1 ratio) to an SpO_2_ target of either 88%–92% or ≥96% while intubated with an endotracheal tube. Clinical teams can adjust FIO_2_ and ventilator settings as they wish to achieve these targets. Clinical information will be collected before, during and after the intervention and blood samples taken to measure markers of systemic oxidative stress. The primary outcome of this study is feasibility, which will be assessed by recruitment rate, protocol adherence and withdrawal rates. Secondary outcomes will include a comparison of standard critical care outcome measures between the two intervention groups, and the measurement of biomarkers of systemic oxidative stress. The results will be used to calculate a sample size, likely number of sites and overall length of time required for a subsequent large multicentre RCT.

**Ethics and dissemination:**

This study was approved by the London - Harrow Research Ethics Committee on 2 November 2017 (REC Reference 17/LO/1334) and received HRA approval on 13 November 2017. Results from this study will be disseminated in peer-reviewed journals, at medical and scientific meetings, in the NIHR Journals Library and patient information websites.

**Trial registration number:**

NCT03287466; Pre-results.

Strengths and limitations of this studyThis is the first study of permissive hypoxaemia in critically ill patients in a National Health Service setting.It is a small randomised controlled trial (RCT) to assess feasibility and not the efficacy of the intervention.The study will compare levels of biomarkers of systemic oxidative stress between the two intervention groups.It will provide valuable information to enable the design of future large-scale RCTs.

## Introduction

In the UK there are over 190 000 admissions to adult critical care units each year (www.icnarc.org). Approximately 40% of these patients will require mechanical ventilation and the mortality rate in this group is approximately 30%.^1 2^ Hypoxaemia is common among this cohort of patients and we lack evidence-based guidelines for their management, particularly regarding what levels of arterial oxygenation are acceptable or optimal. It has been proposed that attempting to fully reverse hypoxaemia in critically ill patients may pose a greater risk of harm than allowing moderate hypoxaemia to persist, a concept called permissive hypoxaemia.^3^ The premise behind permissive hypoxaemia is that the interventions used to correct hypoxaemia may themselves cause harm, in particular high concentrations of inspired oxygen, therefore safely minimising their use could be beneficial.^4–7^

Oxygen has the potential to cause harm when used in high concentration, primarily via its toxic effect on the lungs.^8–10^ Reactive oxygen species (ROS) released mainly from the inner mitochondrial membrane during oxidative phosphorylation serve an essential role in cellular signalling but in excess these highly reactive molecules are able to destroy lipids, proteins and DNA. Their rate of release is determined by cellular oxygen tension^11^ and the extent of damage caused by them can be measured by evaluating biomarkers of tissue degradation.^12^ The lung parenchyma is particularly susceptible to oxygen toxicity in critically ill patients as a result of being exposed to high concentration oxygen during mechanical ventilation. The threshold above which harm may be caused (in terms of concentration and duration of exposure) in critically ill patients is unclear, but since lung injury is common in this patient cohort the threshold may well be lower than in other patients or healthy volunteers. During critical illness the propagation of proinflammatory pathways, with the activation of leucocyte and vascular endothelial responses further increase the ROS burden.^13^ This depletes endogenous antioxidants, which normally regulate ROS homoeostasis.^14^ As a consequence, oxidative stress is a key mechanism of injury in systemic multiorgan failure, and has been linked to increase in morbidity and mortality in critical illness.^15 16^

Oxygen is a drug with a relatively narrow therapeutic index. It should therefore be prescribed, administered and monitored in a manner comparable to other drugs that have toxic side effects. There appears, however, to be wide variation in practice regarding its use and opinions about oxygenation in the critically ill.^17 18^ This is perhaps the result of a paucity of evidence from robust clinical trials; a somewhat surprising situation given that almost every patient admitted to a critical care unit will receive supplementary oxygen. The traditional teaching that hypoxaemia must be avoided at all costs, may have led to a disregard to the potential harm caused by excessive oxygen, and this requires evaluation.

A small number of studies have begun to explore permissive hypoxaemia as a viable treatment strategy in the critically ill, primarily assessing feasibility and safety. In the first study of its kind, 105 mechanically ventilated patients were assessed in a before (n=51) and after (n=54) design.^19^ Following a period of standard oxygenation practice in a single centre (aiming for normal or high blood oxygen levels), a practice change was initiated in which oxygen saturation (SpO_2_) was maintained at 90%–92%. The authors of this study concluded that the conservative oxygen therapy intervention was feasible and free of adverse biochemical, physiological or clinical outcomes. A comparable strategy was used on a much larger scale in a two-stage model, moving from normal oxygenation to an SpO_2_ of 92%–95%.^20^ These authors reported that mechanical ventilation time was significantly lower during both study (lower SpO_2_) phases compared with baseline. The adjusted intensive care unit (ICU) mortality and ICU-free days did not significantly differ between study phases but mortality decreased in reference to baseline for both of the low SpO_2_ phases. In the first multicentre randomised controlled trial (RCT) of permissive hypoxaemia a total of 103 mechanically ventilated patients were allocated to either a conservative oxygenation group (SpO_2_ of 88%–92%) or a liberal oxygenation group (SpO_2_ of greater than or equal to 96%).^21^ The purpose of the study was to confirm feasibility and this was demonstrated, along with no excess of adverse events, in the low SpO_2_ group. The most recently published trial of permissive hypoxaemia was a single-centre RCT that compared SpO_2_ targets of 94%–98% versus 97%–100%.^22^ The primary outcome of this study was ICU mortality, and the values reported were: 11.6% in the conservative group and 20.2% in the conventional group, giving an absolute risk reduction of 8.6% (1.7%–15.0%). This study had a number of limitations^23^ but still adds weight to the argument that permissive hypoxaemia appears to not be harmful and may be of benefit.

A factor of great importance to the design of future studies is selecting the correct ‘standard’ treatment group, in order that the comparison to an intervention of lower oxygenation is valid and meaningful. Different studies have approached this in different ways (either by aiming for an oxygenation target or by determining the administered concentration of oxygen). We hope this feasibility will evaluate our selected methodology and allow us to compare it to other approaches that have been used. We also hope the results of this study will allow us to understand more about other issues specific to critically ill patients such as the concomitant presence of anaemia, low cardiac output and acute respiratory distress syndrome and chronic obstructive pulmonary disease.

## Methods

The trial was designed according to the Standard Protocol Items: Recommendations for Interventional Trials statements.^24^

### Trial aim and objectives

*The Targeted OXYgen therapY in Critical illness* (TOXYC) study aims to determine whether reducing the SpO_2_ target in patients requiring mechanical ventilation is feasible (in terms of participant recruitment and delivery of the intervention) in a National Health Service setting. In doing this we hope to inform future investigators who wish to construct larger trials in this field. The objectives are to construct an RCT of conventional oxygenation versus permissive hypoxaemia, identify any potential barriers to research in this field and explore biological mechanisms that may explain the proposed benefits from the intervention. The project was favourably supported at the UK Critical Care Research Forum in 2016.

### Primary outcome measure

The primary outcome of this study is feasibility, which will be assessed in the following ways: (1) The ability to recruit patients (recruitment rate). (2) Protocol deviations. (3) Rate of withdrawal from the study (in both the intervention and control groups). (4) The reasons for any withdrawal from the study.

Feasibility of recruitment will be evaluated by monitoring patient screening and subsequent agreement to participate, along with any withdrawal of consent during or after the study. Implementation of the study protocol will be evaluated by analysing adherence to oxygenation targets and completion of the treatment without protocol deviations. Reasons for withdrawal will be assessed by the trial management group at the end of the study to assess whether there are common themes that can be addressed in the future.

### Secondary outcome measures

Measurements of oxidative stress (including 4-hydroxynonenal, protein carbonyls, total antioxidant capacity and glutathione reductase) will be made in blood samples taken from participants, in order to understand the potential biological mechanisms that link blood oxygen levels to clinical outcomes. In addition, routine clinical data and outcome measures will be collected from the participants to assess any adverse effects caused by the intervention. Finally, length of critical care stay, length of hospital stay, and survival at critical care unit discharge, 30 days and 90 days will be collected. This information will be essential for the design of future larger trials.

### Trial design

TOXYC, a multicentre RCT, which will be conducted at two sites, is a trial of targeted oxygen therapy in adult critically ill patients receiving mechanical ventilation via an endotracheal tube. Sixty patients will be allocated on a 1:1 basis to either a normal SpO_2_ target group or a lower than normal SpO_2_ target group. A flow diagram of the study is shown in figure 1. Recruitment began in February 2018 and is planned to continue for 15 months.

**Figure 1 F1:**
[figure not shown]
Study flow diagram. PIS, patient information sheet.

### Selection of participants

#### Screening

Screening will occur as part of routine research activity on the two critical care units involved in the study. Research nurses will use medical notes to determine initial suitability for the study, according to the inclusion and exclusion criteria. No additional tests or examinations will be required to ascertain whether patients are eligible for the study. Screening will occur as patients are admitted to the critical care units to minimise the time from admission to enrolment.

#### Inclusion criteria

Unplanned admission to a critical care unit.18 years of age and above (no upper age limit).Respiratory failure forms part of the admission diagnosis.Enrolled within 24 hours of admission (if already intubated) or within 24 hours of intubation (if intubated on ICU).The patient is expected to receive mechanical ventilation for >72 hours.

#### Exclusion criteria

Admission following surgery (elective or unplanned).Those patients expected to die within 24 hours of admission to ICU.Pregnant women.Admission postcardiac arrest.Patients with chronic lung disease known (or highly suspected) to have baseline SpO_2_ in the range of the intervention arm (ie, 88%–92%).Admission post-trauma (including traumatic brain injury).Known sickle cell trait or disease.Ongoing significant haemorrhage or profound anaemia.Severe peripheral vascular disease.Severe pulmonary hypertension.Other medical conditions where mild hypoxaemia would be contraindicated.Patients participating in other interventional clinical trials.

### Enrolment

#### Consent

Due to the severity of illness of the patients being recruited to this study, and the use of sedative drugs that are required for mechanical ventilation, it is unlikely that potential participants will have capacity. Should a potential participant be deemed to have capacity they will be approached by the research team, given a patient information sheet (PIS) and then provided with an opportunity to ask questions. After an appropriate length of time, the research team will seek informed consent from the patient if they wish to participate.

If the patient lacks capacity to provide informed consent, a Personal Consultee (PeC) will be appointed to represent them. This could be the patient’s next of kin, a relative or close friend with whom to discuss the patient’s participation in the trial. The research team will seek the PeC’s opinion as to whether the patient would wish to take part in the trial, providing for them an appropriate version of the ethically approved PIS. If the PeC believes the patient would have wanted to participate in the study (or would not have objected to it), they will be asked to sign a PeC agreement form. If there is no PeC present or immediately available in person, opinion may be sought from a suitable person via the telephone and then a telephone agreement form completed by a member of the research team.

If there is no identifiable PeC for a potential participant then they will be provided with a Professional Consultee (PrC), who is completely independent of the study. Their opinion will be sought as to whether it is appropriate for the patient to be enrolled into the study. Opinion will be sought in the same manner as for the PeC, involving the appropriate version of the ethically approved PIS.

Adequate time will be given for consideration by the patient or PeC/PrC to consider the information in the PIS and ask questions. The research team will record when the PIS has been given to the patient or their consultee. Due to the nature of this patient cohort (critically ill patients requiring substantial organ support due to the severity of their illness) the length of time from identifying a potential participant to initiating the intervention is likely to be less than 24 hours. This is to avoid dilution of the intervention or control effect prior to its commencement.

If a participant who lacked capacity at the point of recruitment subsequently becomes able to provide informed consent (because they gain capacity on recovery from their illness), they will be informed about their participation in the study, provided with a PIS and asked whether they would be willing to provide retrospective consent. At this point the participant will be given the opportunity to withdraw from the study and to decide if the data (and blood samples) collected from them can be included in the final analysis.

All patient consent and consultee agreement procedures will adhere to the Mental Capacity Act (2005).

#### Randomisation

Randomisation will be carried out online after a patient has been recruited to the study and an agreement form or consent form has been signed. It will be conducted in a 1:1 manner for the intervention and control groups, stratified by study site, using random permuted blocks of different sizes. The process of randomisation will be conducted online (www.sealedenvelope.com).

#### Withdrawal

Participants will be withdrawn from the study if:The responsible clinician deems it inappropriate for treatment to continue due to a change in the patient’s condition.The chief investigator or delegated member of the research team deems it inappropriate for treatment to continue due to a change in the patient’s condition.Agreement for the patient to participate in the study is withdrawn by the PeC or PrC.The patient regains capacity and chooses to withdraw from the study.

As this is a feasibility study, patients withdrawn from the study will not be replaced, but the reason for withdrawal will be recorded.

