#### Duration of treatment

The aim is for the intervention to be commenced as soon as possible after admission to the critical care unit (following enrolment) and end following removal of the participant’s endotracheal tube. Specific treatment end points for both groups would therefore include (1) Extubation. (2) Formation of a tracheostomy. (3) Transfer to another critical care unit. (4) Death. The research team will review enrolled participants daily to monitor adherence to SpO_2_ targets and provide bedside advice where required. No targets or limitations will be set for arterial PaO_2_ of oxygen (PaO_2_) or carbon dioxide (PaCO_2_). Should a patient in the study be transferred out of the ICU for a short period of time (eg, for an investigation or intervention) the protocol will be paused until their return. While out of the ICU the clinical team will be in control of the patient’s oxygenation. Should a patient’s condition deteriorate to such an extent that either the clinical or research team feel it not in the patient’s best interest to continue in the study, they will be withdrawn from it at that point.

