#### Follow-up

Length of ICU stay.Length of hospital stay.30-day and 90-day survival rates, and days alive out of hospital.Adverse events.

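### Stopping the allocated SpO2 target for a change in the patient's condition is defined as withdrawal from the study, which puts outcome follow-up of deteriorating patients at risk and pools two kinds of event in the headline withdrawal rate

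*Protocol article*

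**What the plan says.** The Withdrawal section of the protocol article gives four reasons for withdrawal under one heading. The first reads "Participants will be withdrawn from the study if:The responsible clinician deems it inappropriate for treatment to continue due to a change" in the patient's condition. The second gives the same power to the chief investigator or a delegate. The third is of another kind: "Agreement for the patient to participate in the study is withdrawn by the PeC or PrC". The fourth is the choice of a patient who has regained capacity. Withdrawn patients are not replaced, and the reason is recorded.

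The Duration of treatment section repeats the rule for deterioration. If either team judges that going on is not in the patient's "best interest to continue in the study, they will be withdrawn from it at that point". The same section has a separate category for the end of treatment: "Specific treatment end points for both groups would therefore include (1) Extubation", followed by tracheostomy, transfer to another unit and death. Stopping because of deterioration is not in that list.

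The third component of the primary outcome is "Rate of withdrawal from the study (in both the intervention and control groups"). The fourth is the reasons for withdrawal. The Follow-up section lists "30-day and 90-day survival rates, and days alive out of hospital", with length of stay and adverse events, and does not mention withdrawn patients.

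**The concern.** Two different events share one label. In the first, the team takes the patient off the allocated target; in the second, the patient or consultee ends participation. Only the second needs to limit data collection. By calling the first a withdrawal from the study, the text invites site staff to stop collecting data when the target is stopped.

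Any resulting loss would not be random. The stated trigger is a change or deterioration in condition, so the patients concerned probably have a worse prognosis. The Intervention section says that neither the clinical nor the research team can be blinded, so the threshold for withdrawing a patient could differ between arms. An arm could then look safer because more of its failing patients had left the count.

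Two uses of the data are exposed. The Secondary outcome measures section collects clinical data and outcomes partly to detect harm from the intervention. The Statistical design section uses the results to size a later multicentre trial, so an understated event rate would carry forward. Separately, a single withdrawal rate does not by itself show whether the obstacle is the acceptability of the study or the deliverability of the target.

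**Working it through.** **Figures in the plan.** There is none to reproduce. The article reports no sample size calculation and plans no hypothesis test. The check is a comparison of the text, then an illustration of how large the bias could be.

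**Comparison of the text**

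1. Does stopping treatment for a change in condition count as study withdrawal? Yes, in both the Withdrawal and the Duration of treatment sections.
2. Was a category available for ending treatment without leaving the study? Yes, the treatment end points. A patient transferred to another unit reaches an end point; one who deteriorates on the target is withdrawn from the study.
3. Does the article say that follow-up ends at a clinical withdrawal? No. Does it say that follow-up continues? Also no. The only rule on data after withdrawal is in the Consent section. It covers patients who regain capacity, and data and samples already collected from them.
4. Can the two kinds of event be told apart in the primary outcome? Not from the rate alone: 6 withdrawals in 60 patients is 6/60 = 10% whether all six are clinical stops or all six are withdrawals of agreement. They can be told apart from the reasons, which are a primary component and are reported overall and per arm.

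**Illustration of the bias, if withdrawn patients' outcomes are not collected**

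Inputs from the article:
- 60 patients allocated 1:1 (Trial design), so about 30 per arm.
- Mortality of about 30% in ventilated patients (Introduction), used here as a stand-in for trial mortality: p = 0.30, or 9 deaths in 30.

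Assumptions not in the article:
- w, the share of an arm withdrawn for deterioration: 5% to 20%.
- m, mortality among those withdrawn: 50% to 90%.

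Mortality among the patients retained is (p − w × m) / (1 − w).

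| w | m = 50% | m = 90% | Understatement of 30% |
|---|---|---|---|
| 5% | (0.30 − 0.025)/0.95 = 28.9% | (0.30 − 0.045)/0.95 = 26.8% | 1.1 to 3.2 points |
| 10% | (0.30 − 0.05)/0.90 = 27.8% | (0.30 − 0.09)/0.90 = 23.3% | 2.2 to 6.7 points |
| 20% | (0.30 − 0.10)/0.80 = 25.0% | (0.30 − 0.18)/0.80 = 15.0% | 5.0 to 15.0 points |

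In whole patients, starting from 9/30 = 30.0%:
- 2 withdrawn, both die: 7/28 = 25.0%, which is 5.0 points low.
- 4 withdrawn, 3 die: 6/26 = 23.1%, which is 6.9 points low.
- 6 withdrawn, 4 die: 5/24 = 20.8%, which is 9.2 points low.

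These are errors in the level of one arm. If both arms lost the same numbers, both levels would be too low but the difference between arms would not be distorted. If follow-up continues after the target is stopped, no outcomes are lost and the bias is zero in every row.

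**The case against.** The strongest reply is that the article nowhere says that data collection stops. Some of its text points the other way. The Statistical design section intends days alive and out of hospital to be determined for every patient. It names missing data, non-compliers and withdrawals as separate items. The Data collection section draws on medical records and hospital systems, which remain available after the target is stopped. The article is also condensed, and the full protocol may provide for continued follow-up. This stands. A reader might infer that survival and safety data will be lost, or that mortality will be computed only on patients who stayed in; the documents support neither statement.

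The second reply is that the two kinds of event are not hopelessly mixed. Reasons for withdrawal are a primary component, withdrawal of consent is also monitored under recruitment feasibility, and withdrawals are to be reported with reasons per arm. This stands too. A reader might infer that the primary outcome cannot be interpreted; in fact only the headline rate is pooled.

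The third reply is that the sizes rest on assumed withdrawals and deaths, in a trial with no planned comparison. That is correct, so the figures should not be set against the treatment effect of any other trial.

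What remains is that the article does not merely omit a detail. It states a rule, twice, that turns a treatment decision into a study withdrawal. Examining withdrawals for evidence of bias, as the Statistical design section promises, may reveal a problem but cannot restore outcomes that were never collected.

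**Conclusion.** The point holds as a design weakness in how withdrawal is defined, not as a demonstrated loss of data. Followed literally, the rule puts survival, length of stay and adverse event data at risk in the patients most informative about safety, and possibly to a different degree in each arm. Under the assumptions above, a true mortality of 30% would appear as anything from 28.9% down to 15.0% in an affected arm. That range depends on the assumed share withdrawn, on their assumed mortality, and on their outcomes not being collected; if the outcomes are collected, there is no bias. The pooled withdrawal rate is a lesser matter, because the planned reporting of reasons allows the split to be made. The change is worth making because it is cheap and because outcomes not collected at the time may not be recoverable later. It does not call the trial's feasibility aim into question.

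**What to change.** Leave the clinical decision to stop the target, and who makes it, exactly as they are. Change only what follows from it:

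- Define discontinuation of the allocated SpO2 target, decided by the clinical or research team, separately from withdrawal of consent or consultee agreement. Align the Withdrawal and Duration of treatment sections with these definitions.
- State that a patient who discontinues the target stays in the study and in the arm as randomised. Survival, ICU and hospital stay, and adverse events are still collected from records unless agreement to data collection is withdrawn.
- Report the two rates separately by arm, each with its reasons, in place of the single rate in the third component of the primary outcome.

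The cost is one protocol paragraph, one eCRF field to record which event occurred, and a little more follow-up through records that the trial already uses. No extra visits or tests are needed.
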